#### Statistical analysis

2.3.3

Descriptive statistics (means, standard deviations, and frequencies) were computed on (a) demographic and clinical data of the participants (i.e., age, sex, healthcare profession); (b) standardized usability questionnaires. Exploratory group comparisons were performed. All statistical analyses were performed using Jamovi software (version 2.5, 2024) (29).

Further details on the statistical analysis and results from Phase 3—Living Lab 1 can be found in Crocetto et al. (30).

### Phase 4. Usability study

2.4

Phase 4 consisted of a multicentre, non-CE-marked medical device clinical investigation aimed at assessing the usability of the PRoBio integrated platform, refined based on feedback from the Living Labs.

#### Methods

2.4.1

*Objectives*. Objectives of Phase 4 were:

Primary objective: to evaluate the usability of PRoBio in a group of patients with PD-MCI undergoing a structured 4-week cognitive rehabilitation program delivered by the platform.Secondary objectives: (1) to further explore usability in a digital health context, and to assess the user experience, technology acceptance and cognitive workload during the interaction with PRoBio; (2) to assess the acceptability and compliance with the treatment among patients with PD-MCI; (3) to assess the acceptability of the PRoBio platform among rehabilitation professionals; (4) to evaluate PRoBio's capability to record and analyse psychophysiological parameters via RGB-D camera and wearable sensors; (5) to evaluate PRoBio's capability to collect real-time performance data (accuracy and response times) during cognitive exercises administered via VRRS.Exploratory objective: to investigate the potential cognitive changes after a 4-week cognitive rehabilitation intervention delivered via PRoBio in patients with PD-MCI.

*Study participants*. PwPD have been recruited from outpatients attending the Don Carlo Gnocchi Foundation Rehabilitation Center in Sant'Angelo dei Lombardi and Florence sites, or upon referrals from physicians at other centers previously informed about the study. Patients had to meet the following inclusion criteria: (i) a minimum age of 18 years; (ii) diagnosis of PD according to MDS criteria (1); (iii) Hoehn and Yahr stage I–II (43); (iv) MCI according to Litvan criteria (2); (v) provision of written informed consent to participate in the study.

Individuals were excluded if they had: (i) severe depression; (ii) PDD; (iii) atypical Parkinsonism, secondary mixed forms; and (iv) severe behavioral and cognitive disorders associated with other diseases, including delirium and stroke.

*Procedures*. Enrolled patients underwent a comprehensive clinical and neuropsychological assessment to evaluate motor, cognitive, and behavioral functioning at baseline (T0). Following the assessment, all participants were engaged in a 45-min PRoBio-based cognitive training three times per week for four consecutive weeks. The program followed an ABAB design, in which two balanced protocols (A and B, as detailed in Section 2.2.2) alternated on a weekly basis. Every week for each protocol, the complexity of the exercises was modified based on the patient's performance during the last session of the previous week to ensure a tailored difficulty improvement on a weekly basis. At the end of the 4-weeks treatment (T1) patients completed the usability and acceptability questionnaires and underwent the same clinical and neuropsychological assessment performed at baseline.

Age, sex, educational level, handedness, disease stage according to Hoehn and Yahr criteria (43), disease duration, and the predominantly affected hemi-body were collected for each participant.

*Assessment tools*. Clinical and neuropsychological assessment performed at T0 and T1 included the following standardized tools (for details see Supplementary materials):

- MDS-Unified Parkinson's Disease Rating Scale (MDS-UPDRS) (44).- Parkinson's Disease Cognitive Rating Scale (PD-CRS) (45).- Stroop Color Word Test (46).- Trail Making Test (TMT) (47).- Parkinson's Disease Questionnaire (PDQ-39) (48).- 15-item Geriatric Depression Scale (GDS-15) (49, 50).- Geriatric Anxiety Inventory (GAI) (51).

At T1, patients completed the set of usability and acceptability questionnaires used in the Living Lab phase (see Section 2.3.2), which have been adapted for patients. An additional Technology Assisted Rehabilitation Patient Perception questionnaire (TARPP-q) (52) was administered to evaluate the patients' perception of technology-assisted rehabilitation. The graphic representation of the usability study procedures is shown in Figure 3.

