**Methods and analysis:**

The OPERA project is a 13-months non-profit, multicentre clinical investigation structured in four phases. Phase 1 (month 2): focus group, involving 23 participants (10 people with PD (PwPD), 5 caregivers, 8 healthcare professionals) to explore usability, expectations and rehabilitation needs. Phase 2 (months 2–7): development of the PRoBio platform, by integrating the “Virtual Reality Rehabilitation System” (VRRS, by Khymeia Group) with the TIAGo robot (by PAL Robotics) to deliver personalized exercises to patients' cognitive profiles, while also monitoring their emotional and physiological state. Phase 3 (month 6): two living labs involving a total of 21 healthy subjects (13 volunteers and 8 rehabilitation professionals) to assess PRoBio's usability in a real setting, with emotional data collection and standardized usability questionnaires completion after use. Phase 4 (months 8–12): usability study assessing PRoBio's usability as the primary objective, involving 10 PD-MCI patients completing a 4-week cognitive rehabilitation program with pre/post clinical and neuropsychological assessments. Descriptive statistics and appropriate inferential tests (parametric or non-parametric) will be applied to usability data, pre/post intervention clinical measures, and physiological and performance data registered by the PRoBio platform (*p* < 0.05).

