Immediately after their interaction with the system, in order to minimize memory bias effects, participants completed questionnaires to explore five main domains: (i) general usability, (ii) user experience, (iii) workload, (iv) acceptance and intention to use, and (v) eHealth-specific aspects. Accordingly, the following validated instruments were administered: (i) System Usability Scale (SUS) (34) as a standardized index of usability; (ii) eHealth UsaBility Benchmarking Instrument (HUBBI) (35) to capture aspects specific to digital health services such as trust, safety, and information quality; (iii) Short Version of the User Experience Questionnaire (UEQ-S) (36) to assess pragmatic qualities of the interaction; (iv) Scales for Perceived Usefulness and Perceived Ease of Use (TAM) (37) to evaluate perceived usefulness and ease of use as predictors of behavioral intention; (v) the Italian version of the Unified Theory of Acceptance and Use of Technology (I-UTAUT—Original version proposed by Venkatesh (38), later adapted for the field of assistive robotics by Heerink (39) and finally translated and validated in Italian by D'Iorio (40)) to measure performance expectancy, social influence, and facilitating conditions; (vi) NASA Task Load Index (NASA-TLX) (41) to quantify multidimensional workload as a potential limiting factor in cognitive rehabilitation. See the description of the questionnaires in the Supplementary materials.

Italian versions were used whenever available, and short-form versions were preferred to minimize respondent burden. Total completion time was 10–15 min. The entire Living Lab session lasted ~1 h, including the initial interaction with the PRoBio system and the subsequent completion of the usability questionnaires by the participants.

Information on age, sex, educational level, handedness preference and professional role (for healthcare professionals) has been collected.

*Sample size*. Based on the methodology of the Living Lab, the estimation of a specific sample size is not mandatory as its primary objective is to explore and optimize the interaction of the user with the platform in a real scenario (42).

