**Figure 3 F3:**
[figure not shown]
Graphic representation of the Usability Study procedures and the data flow within the OPERA project. Clinical and neuropsychological data are collected at baseline (T0), and at the end of the treatment (T1). Usability data are collected at T1. T0, Baseline Assessment; T1, Follow-up Assessment; MDS-UPDRS, Movement Disorder Society—Unified Parkinson's Disease Rating Scale; PD-CRS, Parkinson's Disease-Cognitive Rating Scale; TMT, Trail Making Test; PDQ-39, Parkinson's Disease Questionnaire; GDS, Geriatric Depression Scale; GAI, Geriatric Anxiety Inventory; SUS, System Usability Scale; HUBBI, eHealth UsaBility Benchmarking Instrument; UEQ-S, User Experience Questionnaire-Short version; TAM, Technology Acceptance Model; I-UTAUT, Unified Theory of Acceptance and Use of Technology-Italian version; NASA-TLX, NASA Task Load Index; TARPP-Q, Technology Assisted Rehabilitation Patient Perception Questionnaire.

*Outcome measures*.

Primary outcome: usability of PRoBio assessed by SUS (34).

Secondary outcomes:

Specific aspects of usability of digital health services such as trust, safety, and information quality, measured with the HUBBI (35). User experience, including pragmatic and hedonic quality, measured with the UEQ-S (36) and with the TARPP-q (52). Technology acceptance explored by the TAM (37) and the I-UTAUT (40). Cognitive workload during interaction assessed with the NASA-TLX (41).Acceptability of the PRoBio platform and compliance with the treatment among patients with PD-MCI measured by (a) the number of treatment sessions completed/number of treatment sessions planned, (b) the number of treatment weeks/total number of weeks planned.Acceptability of the PRoBio platform among rehabilitation professionals measured by (a) the mean time for wearable sensors positioning and starting of the system; (b) the number of system errors/warning; (c) the percentage of sessions' completion.Biomechanical parameters (e.g., range and speed of the patient's movement) recorded by the RGB-D camera, and psychophysiological parameters (e.g., respiratory rate—RR, HR, and GSC), measured through wearable sensors during the treatment sessions.PRoBio's capability to collect real-time performance data during cognitive exercises administered via VRRS assessed by the number of output files recorded by PRoBio/number of exercises per session.

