Exploratory outcome: changes in clinical (MDS-UPDRS) and neuropsychological variables (PD-CRS, Stroop Test and Trail Making Test, GDS, GAI), and quality of life (PDQ-39) between the two timepoints T0 and T1.

*Sample size*. The sample size was derived using data from Saric et al. (53), who reported a mean SUS score of 77.5 (IQR: 70–80.625) when evaluating the usability of a sensor-based interactive hand device. Assuming a 95% confidence level and a conservative margin of error of five points, the minimum required sample was 10 participants, increased to 12 to mitigate potential data loss.

Since the primary objective was to assess the system's usability, all participants underwent treatment with the platform, and no control group was enrolled.

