The Usability Study also presents some limitations. First, it involves a relatively small sample size of PD-MCI patients, limiting generalisability. However, this should be sufficient to conduct a preliminary usability analysis of the first refined PRoBio version. According to user-centered design, this version of the platform will undergo further refinement based on the results from the usability study in the clinical setting. In addition, patient-specific factors such as apathy, fatigue, and variability in compliance may influence engagement and adherence to the training. As a matter of fact, in PD-MCI patients, apathy has been shown to be associated with poorer cognitive performance (65). Future studies should take into account motivational and emotional profiles in PwPD to ensure reliable assessment of usability, safety, and clinical outcomes of a new technology (65, 66).

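### The primary SUS score is scheduled only at the end of week 4, so a patient who leaves earlier has none scheduled; enrolling two extra patients does not remove the bias if leaving is related to usability

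*Protocol article*

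**What the plan says.** The Outcome measures in Section 2.4.1 of the Protocol article name SUS as the primary outcome. The Procedures in the same section fix its timing: "At the end of the 4-weeks treatment (T1) patients completed the usability and acceptability questionnaires". The Figure 3 legend agrees: "Usability data are collected at T1". T1 follows a programme of "45-min PRoBio-based cognitive training three times per week for four consecutive weeks", that is 3 × 4 = 12 planned sessions. No SUS is described during treatment or when a patient leaves early.

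The Sample size paragraph arrives at 10 patients, "increased to 12 to mitigate potential data loss". The Abstract describes Phase 4 as "involving 10 PD-MCI patients completing a 4-week cognitive rehabilitation program". Section 2.4.2 plans descriptive statistics for the primary outcome, and Section 2.4.1 states that there is no control group.

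The article also treats incomplete attendance as possible. Sessions and weeks completed, each over the number planned, are secondary outcomes for acceptability and compliance. The Discussion says that "apathy, fatigue, and variability in compliance may influence engagement and adherence to the training".

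**The concern.** The primary objective concerns patients who undergo the programme, not only those who finish it. In a usability study, stopping can itself be a response to the device. If a patient leaves before T1 because the platform is hard to use, the schedule as written obtains no SUS from that patient, and the mean is formed from the remaining, more favourable ratings.

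Recruiting extra patients answers a different problem. It keeps enough scores for the intended confidence interval but adds nothing about the patients who left. The completion ratios would show that patients left, but they are not linked to the SUS result. With one arm and a descriptive primary analysis, no comparison is available in which such a bias might cancel. At stake is whether the reported SUS mean describes all treated patients or only those who reached T1.

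**Working it through.** **Inputs from the article (Section 2.4.1, Sample size).** Mean SUS 77.5 with IQR 70 to 80.625, 95% confidence, margin of error 5 points, 10 patients required, 12 enrolled.

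**Reproducing the planned figure.** The article gives no formula. Taking SD ≈ IQR width / 1.35:
- SD = (80.625 − 70) / 1.35 = 10.625 / 1.35 = 7.87
- n = (1.96 × 7.87 / 5)² = 9.52, rounded up to 10

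The stated 10 is reproduced. Going from 12 to 10 is a loss of 2/12 = 16.7%.

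**What the two extra patients protect.** The 95% half-width (normal quantile) is 1.96 × 7.87 / √n:
- n = 10: 4.88 points
- n = 12: 4.45 points

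With two patients lost, the planned precision is still met. This says nothing about where the interval is centred.

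**Bias if loss depends on usability.** Let k of 12 patients have no SUS, and let g be the gap between the mean of those with a T1 score and the mean that the lost patients would have given. Then

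bias = (k / 12) × g

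The article gives neither a dropout rate nor scores for patients who leave, so k and g are assumptions:

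| Lost (k of 12) | g = 10 | g = 20 | g = 30 | g = 40 |
|---|---|---|---|---|
| 1 | 0.8 | 1.7 | 2.5 | 3.3 |
| 2 | 1.7 | 3.3 | 5.0 | 6.7 |
| 3 | 2.5 | 5.0 | 7.5 | 10.0 |

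If patients with a T1 score average 77.5 (also an assumption) and 2 of 12 are lost, the all-patient mean is 75.8, 74.2 or 72.5 for gaps of 10, 20 or 30 points. A gap of 5 × 12 / 2 = 30 points makes the bias equal to the whole planned margin. With k = 0 or g = 0 the bias is zero.

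**The case against.** Several objections have force.

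- **The article is a condensation.** The full protocol may provide for an assessment at early withdrawal. This stands as a limit: the point is that none is scheduled under the procedures stated here. It does not dispose of the point, because the article does fix the timing of the primary outcome, in the Procedures and again in the Figure 3 legend.
- **T1 is not tied to attendance.** A reader might infer that the result will describe only patients who tolerated all 12 sessions. The text does not say so. T1 is the end of the four weeks, and a patient who missed many sessions could still complete SUS then. The Abstract's reference to patients completing the programme is a summary phrase, not a definition of the analysis set. The gap concerns patients who leave before T1.
- **The bias is not established.** A reader might infer that the SUS result is biased upward. The document gives no dropout rate, reasons or scores. The allowance is for data loss in general, and the Discussion lists apathy, fatigue and compliance as patient-specific factors, not as reactions to a difficult device. Loss for those reasons need not track SUS. The bias is therefore conditional.
- **The Living Labs are not a precedent.** Section 2.3.2 gave the questionnaires "Immediately after their interaction with the system, in order to minimize memory bias effects". That concerns recall delay in single-session visits and has no bearing on early leaving, so the point does not rest on it.
- **A common time point has merit.** One rating after a four-week programme fits the stated objective, and averaging early with late ratings changes the quantity estimated. This is why the T1 mean should be kept, with early ratings shown beside it.
- **The project has ended.** Section 2 states this, so missing early ratings may be unobtainable. It would still be too strong to say that nothing can be done: Section 2.4.2 describes the analysis in the future tense, and a bounding analysis needs no new data.

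**Conclusion.** The point holds as a conditional weakness in a stated collection rule. SUS is scheduled once, at T1, and loss is met only by raising enrolment from 10 to 12. That protects precision but does not correct a mean from which patients are missing for reasons related to usability. If such loss occurs, the expected direction favours the device.

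With 2 of 12 lost, the overstatement is 1.7, 3.3 or 5.0 points for assumed gaps of 10, 20 or 30, so it reaches the planned margin of 5 only at the largest of these. These figures illustrate scale and do not predict the result. They rest on the assumed loss, the assumed gap, and both losses being related to usability.

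**What to change.** **Collection rule.** State that SUS is taken at T1 from every enrolled patient regardless of sessions attended and, for anyone who leaves before T1, right after the last session attended.

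**Analysis.** Keep the T1 mean. Report early-stop scores beside it with the number of sessions attended, and add an analysis of all patients with at least one PRoBio session.

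**Where early scores were not collected.** Report the number enrolled, the number with SUS and the reasons for stopping. Add a sensitivity analysis that assigns a stated range of low SUS values to patients who stopped. Describe the main result as usability among patients who reached T1. The collection rule can still be applied to any later evaluation of the further refined platform that the Discussion foresees.

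**Cost.** One short questionnaire for each patient who leaves early, plus a few lines of reporting. The small downside is that early and late ratings reflect different exposure, so they should be shown separately as well as combined.

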**Figure 3 F3:**
[figure not shown]
Graphic representation of the Usability Study procedures and the data flow within the OPERA project. Clinical and neuropsychological data are collected at baseline (T0), and at the end of the treatment (T1). Usability data are collected at T1. T0, Baseline Assessment; T1, Follow-up Assessment; MDS-UPDRS, Movement Disorder Society—Unified Parkinson's Disease Rating Scale; PD-CRS, Parkinson's Disease-Cognitive Rating Scale; TMT, Trail Making Test; PDQ-39, Parkinson's Disease Questionnaire; GDS, Geriatric Depression Scale; GAI, Geriatric Anxiety Inventory; SUS, System Usability Scale; HUBBI, eHealth UsaBility Benchmarking Instrument; UEQ-S, User Experience Questionnaire-Short version; TAM, Technology Acceptance Model; I-UTAUT, Unified Theory of Acceptance and Use of Technology-Italian version; NASA-TLX, NASA Task Load Index; TARPP-Q, Technology Assisted Rehabilitation Patient Perception Questionnaire.

*Outcome measures*.

Primary outcome: usability of PRoBio assessed by SUS (34).

Secondary outcomes:

Specific aspects of usability of digital health services such as trust, safety, and information quality, measured with the HUBBI (35). User experience, including pragmatic and hedonic quality, measured with the UEQ-S (36) and with the TARPP-q (52). Technology acceptance explored by the TAM (37) and the I-UTAUT (40). Cognitive workload during interaction assessed with the NASA-TLX (41).Acceptability of the PRoBio platform and compliance with the treatment among patients with PD-MCI measured by (a) the number of treatment sessions completed/number of treatment sessions planned, (b) the number of treatment weeks/total number of weeks planned.Acceptability of the PRoBio platform among rehabilitation professionals measured by (a) the mean time for wearable sensors positioning and starting of the system; (b) the number of system errors/warning; (c) the percentage of sessions' completion.Biomechanical parameters (e.g., range and speed of the patient's movement) recorded by the RGB-D camera, and psychophysiological parameters (e.g., respiratory rate—RR, HR, and GSC), measured through wearable sensors during the treatment sessions.PRoBio's capability to collect real-time performance data during cognitive exercises administered via VRRS assessed by the number of output files recorded by PRoBio/number of exercises per session.

Exploratory outcome: changes in clinical (MDS-UPDRS) and neuropsychological variables (PD-CRS, Stroop Test and Trail Making Test, GDS, GAI), and quality of life (PDQ-39) between the two timepoints T0 and T1.

*Sample size*. The sample size was derived using data from Saric et al. (53), who reported a mean SUS score of 77.5 (IQR: 70–80.625) when evaluating the usability of a sensor-based interactive hand device. Assuming a 95% confidence level and a conservative margin of error of five points, the minimum required sample was 10 participants, increased to 12 to mitigate potential data loss.

Since the primary objective was to assess the system's usability, all participants underwent treatment with the platform, and no control group was enrolled.

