#### Cognitive training by PRoBio

2.2.2

Two 45-min PRoBio-based cognitive training protocols (A and B) have been created by selecting cognitive exercises already available on the Khymeia VRRS system. Each protocol consists of 14 exercises, with an equal number of tasks targeting the same cognitive domains (i.e., attention, executive functions, memory, and visuospatial skills) as shown in Table 1. The protocols were designed by selecting exercises according to the type of task and the targeted cognitive component. For each cognitive function, comparable exercises were distributed across the two protocols to maintain balance in terms of duration, sequencing, and input modality (touchscreen or robotic arm). A more detailed description of the protocols and exercises is shown in Supplementary Table 1.

**Table 1 T1:** Brief description of the two rehabilitation protocols (A and B).

**Cognitive domain**	**Protocol A (Khymeia's task name)**	**Protocol B (Khymeia's task name)**	**Modality**
Attention	Find the differences	Attentive matrix	Touch screen
	Car	UFO	Robotic arm
	Umbrella	Connect the point (TMT)	Robotic arm (A)/Touch screen (B)
	Changing color	No changes	Touch screen
	Changing shape	Changing everything	Touch screen
	Reaction times	Reaction times	Touch screen
Executive function	Sequence of shapes	Get money up to 10€/100€/1,000€/1€	Touch screen
	Plannings	Sort the images in series	Touch screen
	Street path	Daily sequences	Touch screen
	Complete the series	Dual category	Touch screen
	Stroop test	Alphanumeric sequencing	Touch screen (A)/Robotic arm (B)
Visuospatial	Find the symmetric item	Recognize the object among many	Touch screen
	Guess the rotation direction	Puzzle	Touch screen
Memory	Words memory	Long term memory	Touch screen

List of the selected specific tasks for each domain and, brief description of the interaction modality used—either touch screen or robotic arm. More detailed information and descriptions can be found in Supplementary Table 1.

TMT, trail making test; UFO, unidentified flying object.

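### Secondary objective 5 asks whether accuracy and response times are captured, but its only measure counts output files, whatever they contain, over a denominator not labelled planned or administered

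*Protocol article*

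**What the plan says.** The fifth secondary objective (Section 2.4.1, Objectives) is "to evaluate PRoBio's capability to collect real-time performance data (accuracy and response times) during cognitive exercises administered via VRRS". Two quantities are named: accuracy and response times.

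The matching entry under Outcome measures in the same section says this capability is judged by the "number of output files recorded by PRoBio/number of exercises per session". No other measure is attached to the objective.

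Other statements that bear on the ratio:

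- Section 2.2.2 fixes the planned content of a session: "Each protocol consists of 14 exercises, with an equal number of tasks targeting the same cognitive domains".
- Section 2.4.1, Procedures, fixes the schedule: "45-min PRoBio-based cognitive training three times per week for four consecutive weeks".
- The compliance outcome names its denominator: "the number of treatment sessions completed/number of treatment sessions planned". The file ratio carries no such label.
- Session completion is an outcome in its own right, under acceptability among professionals: "the percentage of sessions' completion".
- Section 2.4.2 plans descriptive statistics for the secondary outcomes and sets no pass mark for this one. Its artifact and outlier steps are described for the sensor data and are not linked to the file ratio.

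**The concern.** The objective is about values and the measure is about files. A file can exist without holding an accuracy score or a response time, and the ratio cannot tell the two cases apart. A reported 100% would naturally be read as showing that the performance data were captured, yet it would show only that as many files were written as there were exercises.

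The second difficulty is the denominator. The phrase about exercises per session can mean the 14 exercises that make up a protocol or the exercises actually given that day. The two agree only when a session is completed. Where they differ, the planned version mixes recording performance with session completion, which the article already measures separately.

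At stake is whether one of five secondary objectives gets an answer that can be interpreted.

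**Working it through.** **Inputs**

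- Target quantities: accuracy and response times (Section 2.4.1, Objectives).
- Stated measure: R = F / E, with F the output files recorded and E the exercises per session (Section 2.4.1, Outcome measures).
- Planned exercises per session: 14 (Section 2.2.2). Table 1 agrees: 6 attention + 5 executive + 2 visuospatial + 1 memory = 14.
- Planned sessions per patient: 3 × 4 = 12 (Section 2.4.1, Procedures).
- Patients: 10, or 12 with the allowance for data loss (Section 2.4.1, Sample size).

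The article gives no target or expected value for this outcome, so there is no figure of its own to reproduce.

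**Planned volume.** 14 × 12 = 168 exercises per patient; 168 × 10 = 1,680 for 10 patients; 168 × 12 = 2,016 for 12. These are counts of planned records, not the size of an error.

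**Comparison measure.** U = administered exercises with a readable record holding the named values / exercises administered.

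**Does R depend on content?** All 14 exercises are administered and 14 files are written.

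| Hypothetical session | R = F/14 | What was captured |
|---|---|---|
| All 14 files complete | 14/14 = 100% | U = 14/14 = 100% |
| Accuracy present, response time absent in all 14 | 14/14 = 100% | 14 of 28 target values = 50% (if every task yields both) |
| No usable value in any file | 14/14 = 100% | U = 0/14 = 0% |

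R is 100% in every row. More generally, if a fraction p of files is unusable, R stays at 100% and U = 1 − p, so the gap equals p for any p from 0 to 100%. At an assumed p of 10%, U is 90%, which over the full programme is 0.10 × 1,680 = 168 exercises for 10 patients, or 0.10 × 2,016 ≈ 202 for 12. The 10% is an illustration; the article gives no rate.

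**Does R depend on how the denominator is read?** The session stops early and every exercise given is captured.

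| Stopped after | R, planned denominator | R, administered denominator |
|---|---|---|
| 7 | 7/14 = 50% | 7/7 = 100% |
| 10 | 10/14 = 71% | 10/10 = 100% |
| 12 | 12/14 = 86% | 12/12 = 100% |

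This assumes one file per exercise. The same session yields two different values, and the text does not settle which is meant.

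**Duplicates.** If two exercises were lost and two others each left an extra file, R = (12 + 2)/14 = 100% while U = 12/14 = 86%. Whether the system can leave extra files is not stated, so this shows only that the ratio has no rule for them.

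**The case against.** The best defence has four parts.

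1. *The article is a condensed account, and rules on file validity and duplicates belong in a fuller document.* That is fair for the detailed handling rules, and their absence alone would not be a point. But the article does more than leave detail out: it states a numerator and a denominator, and that numerator does not contain the quantities the objective names.

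2. *Empty capture would surface elsewhere.* The Abstract foresees descriptive and inferential analysis of performance data registered by the platform, and Procedures adjusts difficulty weekly from performance. Wholesale loss would probably be noticed. Partial loss, such as missing response times in some tasks, need not be, and neither use enters the outcome assigned to objective 5.

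3. *The denominator is probably exercises administered.* The outcome entry itself speaks of exercises administered via the VRRS, and the compliance ratios use the word planned where that is meant. This is a reasonable reading. With one file per exercise, the 71% example then disappears. It remains a reading, because the denominator itself is unlabelled.

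4. *Nothing can fail.* The outcome is descriptive with no threshold, and session completion and system errors are reported beside it, so a low ratio caused by stopped sessions could be recognised. This stands.

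A reader might go further and infer that the rule, as written, will err in both directions: that restarted exercises write second files and hide losses, and that early stopping is scored as a recording failure. The documents do not support that. They say nothing about restarts or file structure, the low value needs the planned denominator, and without a pass mark there is no failure to declare.

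**Conclusion.** The point holds in a limited form. The content gap follows from the wording alone: objective 5 names accuracy and response times, and its only measure reads 100% for 14 files per session whether they hold all, half or none of those values. The denominator is ambiguous, and the choice moves a session stopped after 10 exercises between 71% and 100%.

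The low value is conditional on the 14 planned exercises being the denominator and on one file per exercise. All scenarios are hypothetical: the article gives no frequency of unusable, duplicated or missing files, nor of stopped sessions, so no actual bias can be estimated.

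The consequence is confined to one secondary, descriptive outcome. The change is worth making because the stated measure cannot answer its own objective and a better-matched one is simple to define.

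**What to change.** Redefine the outcome for objective 5:

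- **Numerator:** administered exercises with a readable record holding non-missing accuracy and, where the task yields it, response time. Each exercise is counted once, however many files it left.
- **Denominator:** exercises administered, stated as such.
- **Reporting:** descriptive, per session and overall, with the raw file ratio kept as an additional line. List which tasks yield a response time.

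A confidence interval allowing for clustering by patient is optional; the plan treats this outcome descriptively and the fix does not depend on it.

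Cost: a wording change to one secondary outcome and some extra processing of recorded files. The article reports that the project has concluded, so re-scoring depends on the output files and session logs having been kept, which the documents do not confirm. If the number of exercises administered cannot be recovered, the report should say which denominator was used and still apply the content criterion to the files that exist. The capture rate may come out lower than the file ratio.
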